**TABLE OF CONTENTS**

1.0 Abstract 3

2.0 Background and Rationale 3

3.0 Objectives 4

4.0 Selection of Patients (Inclusion and Exclusion Criteria) 5

5.0 Registration Procedure 6

6.0 Study Description and Randomization 6

7.0 Technical Description of Chest X-Ray 7

1. Interpretation of Chest X-Ray and CAD 7
2. Annual Screenings 8

10.0 Subject Follow-Up 9

11.0 Records Keeping 9

12.0 Endpoint Assessment 13

13.0 Statistical Analysis Plan 14

14.0 Sample Size Considerations 16

15.0 Cost-Effectiveness 18

16.0 Adverse Events 20

17.0 Data Safety and Monitoring Committee 21

18.0 Patient Consent and Peer Judgment 21

19.0 References 22

20.0 Appendices 24

1.0 **ABSTRACT**

A two-arm randomized clinical trial of 8,000 high-risk asymptomatic people is planned. Study subjects will be randomized with equal allocation to either A) screening with chest x-ray interpreted by chest radiologists using computer-aided detection (CAD), or B) placebo screening chest x-ray. Screening will occur at entry into the study and one annual screen thereafter. Expert-chest radiologists will first record their findings without CAD and then will record their findings with CAD. The primary aim of the study is to report and compare the frequency of advanced-stage lung cancers at the end of the 2 ½ year study between screened and placebo groups. Size and stage are important intermediary outcomes of screening. Logically, screening would need to detect lung nodules as smaller, earlier stage, treatable, lesions compared to lesions diagnosed after symptoms develop. A comparison of the frequency of advanced-stage cancers after screening, compared to no screening, allows us to assess the effect, if any, of screening on reducing the number of advanced-stage lung cancers.

2.0 **BACKGROUND AND RATIONALE**

Lung cancer is a major public health problem. In the United States approximately twenty nine percent of cancer deaths are secondary to lung cancer 1. There is an estimated 160,000 deaths from lung cancer in the United States each year and over 2 million worldwide. Most of these deaths could be avoided if people did not smoke tobacco related products. Unfortunately, worldwide tobacco consumption has not been declining; suggesting lung cancer will remain an epidemic for years to come. The latest statistics show that Ohio incidence rate of tobacco-related lung cancer was 75.4/100,000 and lung cancer death rate was 64/100,000, both higher than the national estimate. Also, Ohio has the 4th highest prevalence of cigarette smoking (27.7% or 3.2 million Ohioans). Based on those statistics, the economic cost to the state of Ohio is estimated at more than 5 billion per year.2, 3

A high proportion of individuals with lung cancer present at an advanced stage, leaving the overall prognosis very poor once it has been detected. Just over 1 in 8 lung cancer patients will be living 5 years after their diagnosis. Such a dismal prognosis remains despite major efforts in all fronts of the fight against lung cancer (prevention, detection and treatment). The development of an effective lung cancer screening program in which imaging could play a central role would be a major public health achievement.

The earliest efforts at radiographic screening were from the analysis of mass chest x-ray (CXR) screenings from the population of an individual city. This was followed by large controlled studies in the 1970’s that used CXR, sputum, or a combination of the two, as screening tools. Despite considerable ongoing debate about the design and analysis of these randomized studies, they have been interpreted as not showing that screening with plain CXR and/or sputum examination has a beneficial effect on mortality from lung cancer. 4

Given the disappointing overall results from CXR as a screening technique to date, more recent efforts have centered on the use of low-dose CT imaging as a screening tool. Multiple cohorts of at risk subjects screened with chest CT have been reported. Important highlights of these studies include the ability to find many early stage lung cancers, and lengthy survival of those diagnosed with an early stage lung cancer. Difficulties identified in these studies are an inability to comment on lung cancer specific mortality, a large number of benign nodules being identified (5-50% of participants on the initial chest x-ray), intense testing protocols required to follow the identified nodules to ensure they are not cancer, invasive procedures performed on some benign nodules, and questionable cost-effectiveness. 5-13

As it is still to be proven whether CT screening will reduce overall and disease-specific mortality, current guidelines do not recommend lung cancer screening for asymptomatic individuals at risk for lung cancer. Individual patients at risk for lung cancer are being advised of their risk and educated about the current state of early detection. If testing is to occur, it should be in a trial setting in which multidisciplinary specialty groups exist. 14, 15 Two large randomized controlled trials of CT screening are ongoing. These should answer many of the remaining questions about screening for lung cancer with chest CT imaging.

An alternative approach to CT screening would be the use of chest x-rays that have an improved capability in detecting lung cancer. On one hand, chest x-rays have the advantage to be readily available, less costly and subjecting the patients to less radiation. On the other hand chest x-rays may not be as sensitive as CT’s in detecting small cancers. The factors that may contribute to missing a lung cancer on a conventional chest x-ray are related to lesion characteristics and location, technical factors and reader’s perception and errors. Interpreter performance and level of expertise play an important role in the detection and diagnosis of lung cancer.

The role of CAD as applied to chest x-rays is to minimize the potential errors by the interpreter and to identify potential cancerous lesions that can be missed. By improving the accuracy and consistency of radiological diagnosis, CAD will assist the radiologist in detecting early disease that can be potentially missed, allowing for early intervention and management16. We propose to use one of these systems in a screening setting. This will be the first controlled trial of chest x-ray screening in which there is a placebo control group, and the first chest x-ray screening trial that uses CAD to improve our ability to detect subtle cancers.

3.0 **OBJECTIVES**

3.1 **PRIMARY OBJECTIVE**

The primary aim of the study is to report and compare the frequency of advanced-stage lung cancers at the end of the 2 ½ year study between screened and placebo groups.

3.2 **SECONDARY OBJECTIVES**

The secondary aims are as follows:

- Determine whether lung cancer screening with chest x-rays and computer aided detection (CAD) reduces the incidence of symptomatic advanced lung cancer compared to no screening in a high-risk population. The presence of advanced symptomatic lung cancer will be determined by the Outcomes Review Committee.
- Compare the disease-specific mortality between screening with chest x-ray and CAD versus no screening. This is the endpoint used in many RCTs of lung cancer screening; thus, we will be able to compare our study results to the results of these other trials.
- Compare the all-cause mortality rate between screening with chest x-ray and CAD versus no screening. This endpoint includes all deaths including those attributed directly and indirectly to screening.
- Compare the length of time between randomization and the incidence of symptomatic advanced lung cancer for screened subjects versus controls. This analysis will provide data about how screening might delay the development of advanced lung cancer.
- Measure the monetary cost relative to the quality of life between screening with chest x-ray and CAD versus no screening. The comparison of quality of life since randomization between the two study arms will reveal differences over time due to screening. Coupled with an assessment of monetary costs, cost-utility of screening will be measured. Note that the cost-utility analysis will be performed on a subset of the study participants.

4.0 **SELECTION OF PATIENTS**

A 12-month accrual phase is planned. However, if we do not meet our accrual goal within 12 months, we will continue to enroll until March 31, 2010 or until our accrual goal is met; whichever happens first. Participants enrolled after December 31, 2009 will receive one screening at baseline; no incidence screening is planned for these participants. We anticipate enrollment of 8,000 participants.

4.1 **RECRUITMENT**

Recruitment strategies and methods will vary across sites, depending upon specifics of subject’s demographics and resources. All advertisements will be reviewed and approved by the IRB before implementation.

4.2 **INCLUSION CRITERIA**

The **inclusion** criteria for the study are as follows:

1. Ages 40-75 years and at least one of the following criteria…

(a) a current or ex-smoker with at least a 10 pack years history

(b) has first degree family member (parent, sibling, or child) with a history

of lung cancer

(c) has a diagnosis of Chronic Obstructive Pulmonary Disease (COPD)

2. Subject is able to return to the CCHS for annual follow-up screening.

3. Subject is willing to sign a medical release form.

4.3 **EXCLUSION CRITERIA**

The **exclusion** criteria are as follows:

1. Within the last 6 weeks, subject has had:

(a.) A new cough or chronic cough that has gotten worse

(b.) Either new shortness of breath, or any worsening of shortness of

breath

(c.) A cough producing blood

(d.) Constant chest pain

(e.) Respiratory infection, pneumonia, or cold

(f.) Unintentional and unexplained weight loss greater than 5% of total

body weight

2. Subject’s current health condition requires oxygen.

3. Subject has a medical condition that would prevent the subject from

undergoing treatment for lung cancer (e.g. uncorrectable, untreatable heart

condition, cirrhosis of the liver, HIV or AIDS)).

4. Subject has been diagnosed with a malignancy within the last 5 years,

excluding non-melanoma skin cancer, carcinoma in situ of the cervix and

localized prostate cancer

5. Subject has received a chest x-ray or CT within the last 6 months.

6. Subject is participating in another cancer screening trial.

7. Subject has had a pneumonectomy.

8. Subject has had a Lobectomy or Segmentectomy of the lung

within the last 5 years.

9. Subject is participating in an investigational drug or device study, a cancer

screening study, or a cancer prevention study (other than a smoking cessation

program)

5.0 **REGISTRATION PROCEDURE**

People interested in the study will be asked to call a toll free number, [name]. Trained phone interviewers will be available to take these calls, provide a general description of the study and its goals, answer questions about the study, complete the detailed exclusion/inclusion criteria questionnaire, and schedule a baseline visit for eligible subjects. Eligible subjects will be sent a copy of the informed consent document to read prior to their scheduled appointment.

Eligible subjects will be scheduled for a baseline visit at various accrual areas within Cleveland Clinic Regional Healthcare Centers.

6.0 **STUDY DESCRIPTION AND RANDOMIZATION**

At the baseline visit, subjects will be asked to sign the consent form. The baseline study forms (see table 1) will then be administered by the study trained research personnel and entered online. After the completion of the baseline study forms, subjects will be randomized using an online randomization program. The study trained research personnel will log into a website, secured by passwords, to randomize patients. Study subjects will be randomized with equal allocation to either A) free screening with a chest x-ray interpreted by chest radiologists using computer-aided detection (CAD) or B) placebo screening chest x-ray. The subject’s randomization assignment will be determined by the program and recorded into the database. The allocation assignment will not be displayed. Rather, a randomization number will be displayed. The study trained research personnel will print the randomization number and give it to the trained radiology personnel. In the chest x-ray rooms, there will be a paper list which maps the randomization numbers to the study arms (i.e. chest x-ray or placebo). The trained radiology personnel will locate the randomization number on the paper list and determine whether the subject is to receive a chest x-ray or placebo. In this way both the study subjects and study trained research personnel will be blinded to the subjects’ study arm allocation.

A 4-variable stratified randomization design will be applied based on the following stratification variables: site of enrollment (main campus, east, west, or south), age (<65 –versus- >65 years of age), gender, and symptoms status (no reported chronic cough or shortness of breath -versus- reported chronic cough or shortness of breath). A blocked stratified randomization scheme will be used. There will be 8 strata within each enrollment site: 2 ages x 2 genders x 2 symptom statuses (total of 32 strata). Within each stratum we will use a randomized block size of variable size for that stratum.

7.0 **TECHNICAL DESCRIPTION OF CHEST X-RAY**

Patients selected to undergo a chest x-ray will be subjected to the standard procedure in which a frontal view would be obtained. The test will be performed at different locations using digital equipment that is available throughout the Cleveland Clinic Health System (CCHS).

The standard technical factors will be:

PA View

125kVp

1.60mAs

500ms

Left and right AEC sensors

72” SID

The radiation dose to the patient is 20 millirems for the frontal view (PA). That is less than a 6% of the yearly radiation dose that every person is exposed from normal background radiation (360 millirems). It should also be noted that the radiation generated by the chest x-ray procedure is limited to the chest organs while the background radiation affects the whole body.

Patients that will be selected to be in the control group will be introduced to a chest x-ray room and be placed against the x-ray unit however no exposure will be triggered and no image will be obtained. There will be no radiation exposure to the patient.

8.0 **INTERPRETATION OF CHEST X-RAY AND CAD**

Chest x-rays will be interpreted by chest-radiologists. The radiologist will first read the case without CAD, and then with CAD. The findings will be reported by the radiologist on the Radiology Reading Form (case report form), which includes reader findings and recommendations for follow-up. If the radiologist does not find an actionable nodule and does not recommend follow-up for the subject, then the images will be read by a second chest radiologist. This second reading will be blinded to the first interpretation. The findings will be reported by the second radiologist on Radiology Reader Form (case report form). Subjects who underwent a chest x-ray and were found to have an actionable finding on the chest x-ray by one of the radiologists will be mailed a Findings Report form, along with the dictated medical record reports, via certified mail. The Findings Report form will include all actionable findings found by the radiologist. Chest x-rays will be interpreted and reported within approximately four to six weeks of the chest x-ray, and subjects with actionable findings will be notified shortly thereafter.

Subjects with actionable findings will be phoned after written notification to answer any questions the subject has, and to encourage a follow-up visit with a primary care physician or pulmonologist. The recommendations of the radiologist will not be mandated to the subject’s physician; rather, subjects and their physicians together will determine the plan for follow-up testing and treatment, as appropriate.

Subjects with no primary care physician will be offered a list of physicians who could receive the results of their positive screening and oversee the management of follow-up recommended as a result of screening. Under-insured participants will be offered information about local sources of financial assistance and health care services. We will limit the number of subjects that are uninsured at baseline to 10% to ensure that the study objectives are not compromised by an inadequate number of subjects who pursue recommended follow-up.

9.0 **ANNUAL SCREENINGS**

Subjects without a diagnosis of lung cancer and who are deemed to be able to undergo treatment for lung cancer if detected (i.e. no medical condition that would prevent the subject from undergoing treatment for lung cancer) will be scheduled for an annual screening (or placebo screening). A study trained research personnel will phone the study subject and set up an appointment. One incident screens/placebo screen per subject is planned.

At this annual visit, the study trained research personnel will administer the annual study forms (see table 1) to the subject and record the data online. The study trained research personnel will then give the radiologist technician the subject’s randomization number. The trained radiology personnel will locate the randomization number on the paper list in the chest x-ray rooms and determine whether the subject is to receive a chest x-ray or placebo.

The chest x-rays from the annual incident screen will be interpreted by chest radiologists. A radiologist will first read the case without CAD, and then with CAD. Subjects who underwent a chest x-ray and were found to have an actionable finding on the chest x-ray will be mailed a Findings Report form, along with the dictated medical record reports, via certified mail. The Findings Report form will include all actionable findings found by the radiologist. If the radiologists does not recommend follow-up for the subject; then the images will be read by a second chest radiologist. This second reading will be blinded to the first interpretation. The findings will be reported by the second radiologist on a Radiology Case Report Form. Chest x-rays will be interpreted and reported within approximately four to six weeks of the chest x-ray, and subjects with actionable findings will be notified shortly thereafter. Subjects and their physicians together will determine the plan for follow-up testing and treatment, as appropriate.

10.0 **SUBJECT FOLLOW-UP**

At the time of study enrollment and at the annual screen, subjects will be given a packet of study forms (see table 1) and a pre-addressed envelope to take home. The study forms are to be completed by the subject at home and returned to the study trained research personnel at six-month intervals. If the study subject does not return the forms within 2 weeks of the scheduled completion date, the study trained research personnel will phone the subject and administer the study questionnaires via telephone. The study trained research personnel will review the study forms for completeness. If the study trained research personnel have questions about the study form, then the study trained research personnel will call the subject for clarification before sending the study form for data entry into the database.

If at anytime during the duration of the study, the subject is diagnosed with lung cancer additional follow-up will be obtained regarding the diagnosis, pathology staging, treatment, complications and mortality at 2 months intervals. This information will be obtained via telephone or mail by the study trained research personel.

11.0 **RECORD KEEPING**

Records will be secured and kept per all institutional, NCI, state and Federal regulations.

11.1 **DATA COLLECTION FORMS**

The forms to be completed by the study subjects are attached as appendices to this protocol.

Potential trial participants will call into the trial hotline number. Trained research personnel will obtain information to screen for possible eligibility and collect contact information for study appointment. The investigator complies and agrees the protected health Information (PHI) collected to identify eligibility of candidates adheres to the following three criteria: is necessary for the purpose of this research, will be used solely for this research, and will not leave The Cleveland Clinic Health System (CCHS).

The authorization for the release of medical information form will be signed by all subjects at the time of randomization. Attempts to obtain the authorization will be made every six months, but will be required yearly. We will be able to capture changes to their medical insurance provider on a yearly basis.

The eligibility form will be completed to confirm that the subject meets inclusion and exclusion criteria prior to enrolling subject into research trial. Patient informed consent will be signed prior to randomization.

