1. The patient has been diagnosed with non-small cell carcinoma, stage II or

higher, or small cell carcinoma, any stage.

2. The patient has experienced a symptom that led them to seek contact with a

physician since the time of the last study visit; or at the time of their next study

visit, the patient has developed a new symptom or a change in a chronic

symptom within the past 6 weeks, that did not yet lead to a doctor's visit.

3. The symptom(s) described in #2 are felt to be related to the diagnosis of lung

cancer as adjudicated by the Outcomes Review Committee.

For the other secondary endpoints, the committee will review the medical records and self-reported symptoms assessment of all deaths and determine if the death is due to lung cancer.

13.0 **STATISTICAL ANALYSIS PLAN**

13.1 **PRIMARY AIMS:**

Analyses will be based on an intent-to-treat perspective. We will test the null hypothesis that at the time of diagnosis the frequency of advanced-stage cancers is the same for screened and unscreened groups; the alternative hypothesis is that the frequency of advanced-stage cancers is different for screened and unscreened groups. These hypotheses will be tested at the end of the two and a half-year study, i.e. after March 31, 2011. The frequency of advanced-stage cancers in the two study arms will be compared using logistic regression analysis. A model will be fit to describe the probability of advanced-stage cancer as a function of the following independent variables: age, gender, symptoms status at the time of enrollment into the study (i.e. symptoms present or not present), study arm, and two-way interactions with study arm. The fit of the model will be assessed using the Hosmer-Lemeshaw goodness of fit test. The coefficients for study arm and interactions with study arm will be assessed, after adjusting for other covariates, using a likelihood ratio test with significance level of 0.05 (two-tailed).

13.2 **SECONDARY AIMS:**

One of the secondary aims of the study is to determine whether lung cancer screening using chest x-rays and CAD reduces the incidence of symptomatic advanced lung cancer relative to no screening. The observed cumulative incidence of symptomatic advanced lung cancer, measured in events per person per years observed, will be compared between the two study arms. The analysis will be carried out from an intent-to-treat perspective.

The incidence rate of symptomatic lung cancer will be estimated as follows

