The following assumptions were made for determining the required sample size for the primary study aim: prevalence of cancer at baseline screen=1%; annual incidence of cancer=0.5%; annual lost to follow-up=10%; 90% of people randomized to screening are compliant at each screening; 12-month recruitment period; 1 incident screen planned for 12 months after the initial prevalence screen; and 85% sensitivity of chest x-ray with CAD. For development of symptoms following the development of preclinical disease, we assume a uniform distribution over 30 months so that the average time is 16 months from development of detectable preclinical disease until development of symptoms. We assume a 70% reduction in the development of advanced-stage cancers if preclinical disease is detected at screening.

*Placebo Arm:*

Based on these assumptions, if N patients are randomized to the placebo arm, then after one year the number of symptomatic, advanced-stage cancers will be:

(1-lost-to-follow-up rate)(prevalence) (rate of development of symptoms over 12 months)(N).

Similarly, at year two the number of symptomatic, advanced-stage cancers will be approximately:

(1-lost-to-follow-up rate)2 (prevalence) (rate of development of symptoms over 24 months)(N)

for those with preclinical disease at the time of enrollment.

In addition, there are

(1-lost-to-follow-up rate)(incidence)(rate of development of symptoms over 12 months)(N’)

symptomatic, advanced-stage cancers from those who develop lung cancer within the first year, where N’=N-(N)(prevalence).

*Screened Arm:*

If N patients are randomized to the screening arm, and if we assume that at the time of baseline screening, 30% of detected preclinical disease is advanced-stage cancer, then the number of detected advanced-stage cancers detected at baseline is M, where

M = (prevalence)(sensitivity) (0.30)(N).

After one year the number of advanced-stage cancers will be approximately:

(1-lost-to-follow-up rate) (prevalence)(sensitivity)(rate of development of symptoms over 12 months) (N-M)(1-risk reduction due to early treatment) for those cancers detected at baseline but still progressed to symptomatic, advanced-stage cancers in one year.

In addition, there are those cancers undetected at baseline that progress to symptomatic, advanced-stage cancers in the first year:

(1-lost-to-follow-up rate)(prevalence)(1-sensitivity) (rate of development of symptoms over 12 months)(N-M).

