We estimate that if the frequency of advanced-stage cancers at two years is 1.19% for controls and 0.77% for the screened arm (difference of 0.42%), then we can detect this difference with 4000 subjects per study arm with 77% power (5% type I error rate, two-tailed test).

15.0 **COST-EFFECTIVENESS ANALYSIS**

The cost effectiveness analysis will be performed only on subjects who declare themselves as Cleveland Clinic patients at entry into the study. The rationale is based on experiences from other studies where it was found to be impossible to collect valid medical visit and hospital stay data from other medical institutions even when the study subject had signed a medical release form. Thus, it was decided that the cost-effectiveness assessment in this study would be limited to Cleveland Clinic patients for whom medical records could more easily and reliably be obtained. We recognize that this decision limits the generalize ability of our cost effectiveness analysis results.

This analysis will be conducted from the US societal perspective as recommended by the U.S. panel for cost effectiveness in health and medicine.24 The initial time horizon will be the three-year study period, but will also be extended to 10 and 20 years using Markov modeling approach to measure the long-term cost-effectiveness difference between lung cancer screening and placebo screening. When data are collected after each visit, the intermediate analysis will be conducted to analyze the short-term cost-effectiveness outcomes if necessary. The results from the intermediate study could be used to guide the concurrent treatment in clinical settings.

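### Entrants after 31 December 2009 have one screen and 12–15 months of follow-up, and modestly dilute a primary comparison that was sized on two-year rates

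*Protocol*

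**What the plan says.** Section 4.0 of the protocol plans 12 months of accrual. If the goal is missed, "we will continue to enroll until March 31, 2010 or until our accrual goal is met; whichever happens first". For the late group it adds: "Participants enrolled after December 31, 2009 will receive one screening at baseline; no incidence screening is planned for these participants". Section 9.0 still plans one incident screen per subject and makes no exception for late entrants.

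Section 13.1 leaves the closing date where it was: "These hypotheses will be tested at the end of the two and a half-year study, i.e. after March 31, 2011". On the population it says: "Analyses will be based on an intent-to-treat perspective". The primary model is a logistic regression of advanced-stage cancer (yes or no) on arm, age, gender, symptom status and interactions with arm. It has no term for length of follow-up.

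Section 14.0 sizes the trial on a 12-month recruitment period and an incident screen at 12 months. Its power statement applies "if the frequency of advanced-stage cancers at two years is 1.19% for controls and 0.77% for the screened arm". It has no term for subjects with one screen and little more than a year of observation.

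**The concern.** A subject randomised between 1 January and 31 March 2010 is observed for 12 to 15 months by the close. Section 14.0 counts 30% of cancers detected at the baseline screen as advanced-stage events at once, in the screened arm only. In the placebo arm, prevalent cancers become events only as symptoms appear, spread uniformly over 30 months. The screened arm therefore starts with a surplus, and prevented cancers repay it over time. A group observed for little more than a year has barely reached the point of repayment.

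If such subjects enter the primary model on the same footing as those with two screens and longer follow-up, they add events without adding contrast. The primary estimate then depends partly on how slowly the trial recruited, and the stated design effect no longer describes the population being analysed.

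**Working it through.** **Inputs (Section 14.0).** Prevalence 1%; annual incidence 0.5%; annual loss 10%; compliance 90%; sensitivity 85%; time to symptoms uniform over 30 months; 70% reduction after detection; already advanced at detection 30% (baseline screen) and 15% (incident screen).

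**Step 1: reproduce the plan's figure.** Table 2 at 4,000 per arm, adding the Section 14.0 terms in order:
- Placebo: 14.400 + 25.920 + 7.128 = 47.4 (stated 47.5).
- Screened: 10.200 + 3.663 + 2.154 + 2.045 + 6.593 + 3.878 + 1.472 + 0.962 = 31.0 (stated 30.9).

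The formulas are therefore read as intended. The year-one terms alone give 14.4 placebo events and 10.2 + 3.7 + 2.2 = 16.0 screened events (sum of the unrounded terms).

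**Step 2: one-screen subjects followed for m months.** Let s = 0.9^(m/12) and r = m/30. The plan gives only 12- and 24-month terms, so values between are interpolated from its uniform assumption. For disease present at entry:
- Placebo = s × 0.01 × r.
- Screened = 0.00255 + s × 0.01 × r × (1 − 0.00255) × (0.85 × 0.30 + 0.15), where 0.00255 = 0.01 × 0.85 × 0.30.

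| Months | Placebo | Screened | Placebo minus screened (points) |
|---|---|---|---|
| 12 | 0.360% | 0.400% | −0.040 |
| 15 | 0.438% | 0.432% | +0.006 |
| Mean, 12–15 | 0.400% | 0.416% | −0.017 |

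The arms cross at about 14.6 months. Applying 90% compliance at baseline as well changes little (0.360% v 0.396% at 12 months).

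**Step 3: do not count baseline-advanced cancers again.** The plan subtracts the baseline-advanced cases from N, not from the detected cancers, so those cancers can progress and be counted twice. Removing them gives screened = 0.00255 + s × r × [(0.0085 − 0.00255) × 0.30 + 0.0015]. The differences become −0.013 points at 12 months, +0.013 at 13.5 and +0.039 at 15. All are small beside the design difference of 1.19% − 0.77% = 0.42 points.

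**Step 4: effect on the whole trial.** Assumptions: start about October 2008 (2½ years before the close) and 8,000 subjects entering evenly over 18 months, so 3/18 = one sixth enter late. Each prevalent cancer is counted once, cumulatively, because Table 2 adds the 12-month count to the 24-month count of the same cancers. First-year incident cancers are added to both arms as s × 0.005 × 0.99 × (m − 12)/30. In the screened arm of two-screen subjects they are split instead into detected (0.90 × 0.85 = 0.765) and undetected (0.235), with 15% of detected cases advanced at once.

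| Analysis | Placebo | Screened | Difference | Ratio |
|---|---|---|---|---|
| All 8,000, calendar close | 27.9 | 23.5 | 4.3 | 0.84 |
| Entry by 31 Dec 2009 | 25.1 | 20.6 | 4.4 | 0.82 |
| Jan–Mar 2010 entrants only | 2.8 | 2.9 | −0.1 | – |
| All 8,000 followed 24 months | 32.3 | 25.7 | 6.6 | 0.79 |

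Differences are taken before rounding. With the Step 3 correction the late entrants give about 2.8 v 2.7.

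**Step 5: does dropping the late group cost power?** Divide the difference by the square root of total events. With late entrants: 4.33/√51.4 = 0.60. Without: 4.45/√45.7 = 0.66. With the Step 3 correction the values are 6.07/√49.6 = 0.86 and 5.98/√44.1 = 0.90. Leaving them out gives slightly more under either count.

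**The case against.** The endpoint is defined to a calendar close, and even the planned 12-month accrual gives 18 to 30 months of follow-up. Unequal follow-up is therefore part of the design. Randomisation balances entry dates, so the arms are not confounded. The extension is conditional: if the goal is met by the end of 2009 there are no late entrants. All of this stands, and it makes the point one of dilution, not bias between arms.

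A reader might infer three stronger things that the documents do not support.
- **Late entrants show a reversed effect.** The plan's formulas give this at 12 months and on average over the window, but not at 15 months. The average reversal disappears once cancers already advanced at baseline are not counted again. What holds either way is that there is practically no expected difference.
- **The primary odds ratio could be carried past 1.** In the scenario above the ratio of expected events moves only from 0.82 to 0.84.
- **The extension costs about 35% of the expected difference.** The figure is (6.6 − 4.3)/6.6, but its comparator is 24 months of follow-up for everyone. At the same recruitment rate, stopping after 12 months would give about 8,000 × 12/18 = 5,333 subjects and an expected difference of about 4.4 events, much the same as with the extension. Most of the shortfall comes from slow accrual.

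**Conclusion.** The concern holds in limited form. Sections 4.0, 13.1 and 14.0 do not fit together: subjects with one screen and 12–15 months of follow-up enter a primary model sized on two screens and two-year rates. By the plan's own inputs they contribute events and practically no contrast.

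Under even 18-month accrual the harm is a shift in the ratio of about 0.02 and about 0.1 expected event of difference. If cancers already advanced at baseline are not counted again, late entrants add about 0.1 event of benefit, yet leaving them out is still slightly more efficient. These sizes rest on an inferred start date, an assumed late share of one sixth, interpolation between the plan's 12- and 24-month terms, and its screening assumptions. This is a should-fix.

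**What to change.** Pre-specify in Section 13.1 that the primary analysis set is all subjects randomised on or before 31 December 2009, analysed as randomised. The date is fixed at baseline and applies equally to both arms, so it introduces no selection after randomisation. Add a sensitivity analysis of all randomised subjects.

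Restate expected events and power in Section 14.0 for the extended-accrual scenario, stating the late share assumed. Power should be recomputed from the start: 1.19% v 0.77% with 4,000 per arm gives about 48% two-sided, not the stated 77%, which is a separate matter.

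The cost is a wording change, up to about one sixth fewer subjects, and fewer events in the primary model. On Table 2's own counting, a one-sixth late share leaves 78.4 × 5/6 = 65.3 events without late entrants, against about 70.8 with them. The former is below the 70 that Section 14.0 asks for, so the number of model terms would need another look.

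A fixed 24-month window for every subject is an alternative only if the sponsor accepts up to a year of extra follow-up (forms, record retrieval, follow-up of diagnosed cases) and a later endpoint review. It would also discard months 24–30 of the earliest entrants.
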